### Data collection

Each participating centre’s personnel involved in treating patients with HD are trained in providing eligible patients with both oral and written information about the study. All the medical baseline and procedure data are collected at the individual hospitals. The data is stored in standardized case record forms (CRFs) within Castor.

The surgeons involved in treating patients with HD are responsible in collecting the data from the initial visit/treatment and the 6-week outpatient visit where complications are scored. Research personnel of each participating centre is responsible for their own data collection during the 6-month follow-up period.

## Statistical analysis

Both intention-to-treat and per-protocol analyses shall be carried out. Crossover is not desirable, but possible if deemed necessary by the treating physician. Crossover will be considered as a secondary outcome measure. Analyses will be carried out using SPSS version 26.0. A *p*-value of 0.05 or less is considered as statistically significant.

For the primary outcome, any reduction in a PROM/PREM score per symptom is scored as ‘improvement’ when considering the results as binary success or not. Analysis of primary outcomes will be tested with chi-square test or Fisher’s exact test. Considering there are four time points for the outcomes, these time points will be taken into account during the analysis. Descriptive methods will be used to check the quality of the data, homogeneity of the two treatment groups and primary and secondary endpoints. Significant confounders will be identified using multivariate analysis. Categorical variables will be presented as percentages and continuous variables will be presented as means with their confidence intervals. To examine gender differences, an additional analysis will be carried out. An interim analysis will take place after the first 300 patients have been randomised and 6-month follow-up is completed. Both the number of patients who experienced complications and the number of patients with recurrent symptoms after 6 months will be evaluated between the two groups. If there are significant differences, then the entire study group will discuss these findings and discuss whether the study can be continued.

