### Eligibility criteria

#### Inclusion criteria

Grade 1 (symptomatic with rectal blood loss) or grade 2 haemorrhoids (Golligher classification)Aged 18 years old or older and legally competent

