	**Tools of measurement**
**Primary outcomes**	
*Patient-related outcomes*	PROM (minimal score 5, maximum score 25): The lower the score the better the result
- Blood loss	Likert scale – 1 (not at all) to 5 (very much)
- Pain	Likert scale – 1 (not at all) to 5 (very much)
- Prolapse	Likert scale – 1 (not at all) to 5 (very much)
- Itching	Likert scale – 1 (not at all) to 5 (very much)
- Soiling	Likert scale – 1 (not at all) to 5 (very much)
	HISS (minimal score 0, maximum score 20)
- Impact on daily activities	Scale – 0 (no impact at all) to 10 (highly impacted on daily activities)
- Satisfaction with treatment	Scale – 0 (not at all satisfied) to 10 (very satisfied)
*Complications*	
Incontinence	Wexner Fecal Incontinence Score
Abscess	Physical examination^a^
Fistulation	Physical examination^a^
Urine retention	Bladder scan
Anal stenosis	Physical examination^a^
Anal fissure	Physical examination
Arterial bleeding	Physical examination
Thrombosed haemorrhoid	Physical examination
*Recurrence*	Subjective return of initial symptoms

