#### Treatment efficacy

This outcome follows the patient-reported outcome measure-haemorrhoidal impact and satisfaction score (PROM-HISS) questionnaire from the international Delphi procedure of the European Coloproctology group, for which recently the first steps in the validation process were taken [10, 11, 13].

This questionnaire consists of three domains: (1) HD symptoms, (2) impact of HD on daily activities, and (3) satisfaction with treatment [13]. The first domain contains five HD symptoms of which each is scored on a Likert scale ranging from 1 (“not at all”) till 5 (“very much”), resulting in a maximum possible score of 25. During follow-up, any reduction in score on this numeric scale is classified as ‘improvement’. This will then be translated into a binary outcome: “yes” or “no” improvement of symptoms. Both the second and third domains only contain one item, the impact of HD on daily activities and patients’ satisfaction with treatment, respectively. Both are scored on a 10-point numeric rating scale. In respect to the impact of symptoms on daily activities, 0 correlates with “no impact at all” and 10 with “highly impacted on daily activities”. On the contrary, for patient satisfaction with treatment, this ranges between 0 “not at all satisfied” and 10 “very satisfied”. Data from the PROM-HISS questionnaire is collected 1 week after the procedure, so the recall period comprises “the past week” [13].

Complications (i.e. incontinence, abscess, fistula, fissure, urine retention, anal stenosis, arterial bleeding or thrombosed haemorrhoid) are scored at the 6–8 week clinical follow-up appointment at the outpatient clinic. Subjective return of initial symptoms (recurrence) is recorded during the 6-month follow-up period.

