#### Secondary outcomes

Secondary outcome measures consist of patient experience outcomes (PREMs), number of treatments, crossover and number of days on work leave.

Patient experience outcomes are recorded on the PREM questionnaire (Appendix). It contains a series of questions regarding the patients’ experience of the treatment, which is partly scored on a Likert scale ranging from 1 (“not at all”) till 5 (“very much”). Two additional binary (yes/no) questions are added regarding whether patients would undergo the same treatment and whether they would recommend the treatment to acquaintances suffering from similar HD symptoms. The administration of this questionnaire takes place 1 week after treatment. The total number of treatments, the crossover of treatment arms and days of work leave are recorded after a total of 6 months of follow-up. All data entries are stored in Castor^EDC^.

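### Binary success for the primary outcome is defined in two conflicting ways, and one of them includes a questionnaire that has no baseline

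*Protocol article*

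**What the plan says.** Treatment efficacy (under Outcomes) describes five symptom items, each scored 1 to 5, "resulting in a maximum possible score of 25". It continues: "During follow-up, any reduction in score on this numeric scale is classified as" improvement, which is then turned into a yes/no outcome. Table 1 gives the same scale as "PROM (minimal score 5, maximum score 25): The lower the score the better the result" and also lists the five symptoms one by one under primary outcomes.

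Statistical analysis, for the same primary outcome, says that "any reduction in a PROM/PREM score per symptom is scored as" improvement when results are treated as binary success.

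The PREM is listed in Table 1 and in the Secondary outcomes section as a secondary outcome. On timing, the latter says: "The administration of this questionnaire takes place 1 week after treatment". Table 2 marks it at 1 week only. Its questions (Appendix) concern pain during and after the procedure, urge afterwards, satisfaction with the treatment, and whether the patient would have it again or recommend it.

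Sample size calculation attaches one success rate of 70% per arm, a 10% margin and 330 patients per arm to symptom reduction. It does not say which of the two rules it means.

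**The concern.** The same binary endpoint is given two scoring rules. The first yields one result per patient from a sum. The second works symptom by symptom and does not say whether that means five endpoints, success if any item falls, or success only if all items fall. It also brings in a questionnaire on which a reduction cannot be calculated.

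At stake is what the non-inferiority conclusion refers to. A margin in percentage points and a sample size built on a 70% rate have meaning only for a defined success. A different rule gives a different success rate, hence different power at 330 per arm, and possibly a different answer from the same data.

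**Working it through.** **1. The two rules applied to one patient** (scores chosen for illustration). Baseline: blood loss 4, other four items 1 each; total 4 + 4 = 8. Follow-up: blood loss 3, pain 3, other three items 1 each; total 3 + 3 + 3 = 9.
- Fall in total: no (8 to 9). Failure.
- Blood loss alone: yes (4 to 3). Success.
- Pain alone: no (1 to 3). Failure.
- Any item falls: success. All items fall: failure.

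**2. The PREM.** A reduction needs an earlier value. The PREM is given once, after treatment, and asks about the treatment itself, so there is no baseline.

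**3. The planned sample size.** Inputs from Sample size calculation: p = 0.70 in both arms, margin 0.10, alpha 2.5% (taken as one-sided, the reading that reproduces the stated figure), power 80%.

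n per arm = (1.960 + 0.842)² × 2 × 0.70 × 0.30 / 0.10² = 7.849 × 42 = 329.7, so 330. The stated figure reproduces.

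**4. Dependence on the success rate.** Power at 330 per arm with equal true rates p is Φ(0.10 / √(2p(1−p)/330) − 1.960).

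| True success rate | n per arm for 80% power | Power at 330 |
|---|---|---|
| 50% | 393 | 72.9% |
| 60% | 377 | 74.6% |
| 70% | 330 | 80.0% |
| 80% | 252 | 89.5% |
| 90% | 142 | 99.0% |

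**5. How far apart the rules could be.** The documents give no item distributions, so this is a simulation on assumptions: 30% or 45% of scores at the floor of each item, correlation between items 0 or 0.4, moderate true improvement, patients with no symptom on any item left out. The total falls in 65–70% of patients, at least one item falls in 81–92%, and a given item falls in 33–41%. In 16–22% at least one item falls while the total does not.

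**6. The floor, only if single items are analysed alone.** A patient at 1 on an item cannot fall. Let f be the share able to improve on that item (assumed), with true success of 70% v 55% among them (assumed). Over all patients the rates are 0.70f and 0.55f, and the gap is 0.15f. P(non-inferiority) = Φ((0.10 − 0.15f)/SE − 1.960), with SE from the two rates at 330 per arm.

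| f | Rates | Gap (points) | P(non-inferiority) |
|---|---|---|---|
| 70% | 49.0% v 38.5% | 10.5 | about 2% |
| 50% | 35.0% v 27.5% | 7.5 | about 10% |
| 30% | 21.0% v 16.5% | 4.5 | about 44% |

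For f = 50%: SE = √((0.35 × 0.65 + 0.275 × 0.725)/330) = 0.0360; 0.025/0.0360 − 1.960 = −1.27; Φ = 0.10.

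With equal true effects (70% among those able, in both arms), the formula in step 4 gives power of 75.8%, 72.9% and 76.8% at f = 90%, 70% and 50%. At f = 30% it rises to 88.4%.

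**The case against.** The best defence is that Treatment efficacy is not fully explicit. The scale it refers to could be stretched to mean the 1-to-5 item scale, and Table 1 shows both the total and the separate symptoms as primary. This stands in part: the total is the natural reading, because the phrase follows directly on the maximum of 25 and leads to one yes/no, but it is not the only possible one. Even so, the text then offers two candidate endpoints and does not choose. On either reading the PREM remains unworkable.

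A full protocol or analysis plan, not shown, may settle the rule. A reader might infer that the investigators are free to choose the definition after seeing the data. The article does not establish that. What it establishes is that its own two statements conflict, which is different from leaving out a detail.

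A reader might also infer that the floor biases the trial towards non-inferiority. The documents do not support that as a general claim. Trial design describes patients whose symptoms were not managed conservatively, and entry is "Grade 1 (symptomatic with rectal blood loss) or grade 2 haemorrhoids", so patients should start above the floor on at least one item. The floor then hardly touches the total or an any-item rule. It matters for an item the patient lacks, analysed alone. There it can shrink a true difference or, with equal effects, lower power; these pull in opposite directions.

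Finally, counting any 1-point fall as success may look like an error. It is a design choice that the article states openly.

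**Conclusion.** The point holds as a contradiction in the text, and that part needs no assumption. Two sections score the same primary outcome by rules that can classify one patient in opposite ways, and one rule includes a secondary questionnaire on which no reduction can be computed. The 70% rate, the 10-point margin and the 330 per arm are therefore not anchored to one endpoint.

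The sample-size arithmetic itself is sound for a single binary endpoint at 70%; the contradiction does not show that 330 is wrong. The size of the consequence depends on which rule is used and on success rates that the article does not give by rule. The simulated rates and the floor figures illustrate this under stated assumptions and are not estimates for this trial.

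This should be settled before analysis, because the primary endpoint carries the non-inferiority claim.

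**What to change.** In Statistical analysis, remove the PREM and the per-symptom wording from the primary rule. Define success there as Treatment efficacy most naturally does: a reduction in the five-item PROM total (5 to 25) from baseline, one yes/no per patient. State in Sample size calculation that the 70% refers to this definition.

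Report per-symptom improvement as supportive, restricted to patients scoring at least 2 on that symptom at baseline. Add a baseline-adjusted comparison of the mean PROM total as a supportive analysis, outside the decision rule.

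The cost is a short text change; at the planned 70% the 330 per arm stands. The downside is that per-symptom results, now listed in Table 1 under primary outcomes, become supportive and use fewer patients. The change leaves the any-reduction threshold as it is. It also does not settle which follow-up visit carries the primary comparison, which is a separate matter.

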**Methods and analysis:**

This protocol describes the methodology of a non-inferiority, multicentre, randomised controlled trial comparing rubber band ligation and sclerotherapy for symptomatic grade 1–2 haemorrhoids in adults (> 18 years). Patients are preferably randomised between the two treatment arms. However, patients with a strong preference for one of the treatments and refuse randomisation are eligible for the registration arm. Patients either receive 4 cc Aethoxysklerol 3% SCL or 3 × RBL. The primary outcome measures are symptom reduction by means of PROMs, recurrence and complication rates. Secondary outcome measures are patient experience, number of treatments and days of sick leave from work. Data are collected at 4 different time points.

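### Two 0–10 items that Table 1 lists as primary have no fitting test: chi-square/Fisher and the any-reduction rule do not suit impact on daily activities or treatment satisfaction, and their primary status needs reconciling

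*Protocol article*

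**What the plan says.** The Primary outcomes section of the Protocol article refers to Table 1 for the list. There, under the primary heading, impact on daily activities is scored "Scale – 0 (no impact at all) to 10 (highly impacted on daily activities") and satisfaction with treatment "Scale – 0 (not at all satisfied) to 10 (very satisfied"). The Treatment efficacy section treats them as the second and third domains of the PROM-HISS questionnaire and adds: "Both are scored on a 10-point numeric rating scale".

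The Statistical analysis section names one family of tests: "Analysis of primary outcomes will be tested with chi-square test or Fisher’s exact test". The sentence before it gives the rule for a binary result: "any reduction in a PROM/PREM score per symptom is scored as ‘improvement’ when considering the results as binary success or not". Treatment efficacy gives a similar rule for the five-symptom score: "This will then be translated into a binary outcome: “yes” or “no” improvement of symptoms". Neither place gives a cut for the two 0–10 items. The Statistical analysis section also says that "continuous variables will be presented as means with their confidence intervals".

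The abstract is narrower than Table 1: "The primary outcome measures are symptom reduction by means of PROMs, recurrence and complication rates".

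**The concern.** A chi-square or Fisher test needs categories. For complications, recurrence and binary symptom success these exist. For the two 0–10 items they do not, so a literal analyst has two options: treat the eleven scores as unordered categories, or choose a cut. The first ignores the ordering, and its test result carries no direction. The second leaves the cut open to choice after the data are seen. Both give up power compared with an analysis on the full scale.

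The any-reduction rule does not fill the gap. It could be stretched to impact on daily activities, where lower is better, if a baseline is collected. It cannot be stretched to satisfaction with a treatment not yet given, and a reduction there would mean a less satisfied patient.

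At stake is how well the trial can compare the arms on these two patient-reported items. The symptom-based comparison that sized the trial is not at stake.

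**Working it through.** **1. Status of the two items, place by place**

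| Place in the Protocol article | What it supports |
|---|---|
| Primary outcomes, Table 1 | Both items under the primary heading |
| Treatment efficacy | Both described as PROM-HISS domains |
| Abstract; Objectives | Primary = symptom reduction, recurrence, complications; neither item named |
| Background and rationale | Patient experience is secondary; satisfaction rates are given as an example of such outcomes |
| Table 2, primary rows | Symptoms, complications, recurrence; neither item |
| Table 2, secondary rows | Satisfaction/experience, labelled PREM |

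Table 1 is the list that the outcome section points to, but the other places do not match it.

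**2. The plan's own figure**

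Inputs from Sample size calculation: 70% success in both arms, 10% margin, alpha 2.5%, power 80%. With alpha taken as one-sided 2.5%:

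n per arm = (1.960 + 0.842)² × 2 × 0.7 × 0.3 / 0.10² = 7.849 × 0.42 / 0.01 = 329.7, so 330.

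The stated 330 per arm is reproduced. It concerns binary symptom improvement and does not depend on the two 0–10 items. It is used below only as the number per arm.

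**3. What a categorical test costs on an ordered scale**

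The protocol gives no SD, distribution or expected difference for these items, so the following is assumption. The test is a two-sided 5% test of difference, because no non-inferiority margin is given for them.

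For a shift of d standard deviations, the noncentrality is λ = 330 × d² / 2. A mean comparison uses λ on 1 df. A 2 × 11 table spreads about the same λ over 10 df. A cut at the median keeps about λ × 2/π on 1 df. A mean comparison has 80% power at d = 2.802 × √(2/330) = 0.218.

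| d | λ | Mean comparison | 2 × 11 table | Median cut |
|---|---|---|---|---|
| 0.20 | 6.60 | 73% | 36% | 54% |
| 0.22 | 7.99 | 81% | 43% | 62% |
| 0.25 | 10.31 | 90% | 56% | 73% |
| 0.30 | 14.85 | 97% | 76% | 87% |

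**4. Simulation with rounded scores**

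Normal scores were rounded and clipped to 0–10, with means from 3 to 8, SD 2 to 2.5 and 330 per arm.

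- Shift 0.22 SD: t-test or Wilcoxon about 76–81%; 2 × 11 chi-square about 38–42%; best-placed single cut about 61%.
- Shift 0.30 SD (mean 5, SD 2.5): t-test 97%, best cut 87%, 2 × 11 about 74%. The loss is about 10 points with the best cut and a little over 20 with all categories (21 by the formula, about 24 by simulation).
- Poor cuts at about 0.22 SD: with mean 3 and SD 2.5, cutting at 8 or more gives 24% against 79% for the t-test, a loss of 55 points.
- Skewed (gamma) scores at 0.218 SD: t-test 72%, Wilcoxon 64%, best cut 55%, 2 × 11 about 32%. The loss runs from 9 points (64 − 55) to about 39 (71.6 − 32.5).

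**The case against.** The strongest reply is that the chi-square sentence directly follows the definition of binary success, so in context it may name the test for that outcome and for the other yes/no primary outcomes only. That reading is possible. But the sentence says primary outcomes, in the plural and without limit, and Table 1 puts two numeric items among them. If the narrow reading is meant, a few words would make it explicit.

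It can also be said that a condensed article leaves test details to the full protocol or analysis plan. That would answer a complaint that a method is missing. Here a method is stated, and it fits two listed outcomes badly.

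Three stronger readings are tempting, and the document does not support them:

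- **That the items are plainly primary.** Only Table 1 and, less directly, Treatment efficacy support this. The Table 2 satisfaction row does not settle it the other way: it is labelled PREM, and the PREM in the Appendix has its own satisfaction item, scored 1–5 in the opposite direction.
- **That the trial could not show which treatment does better on these items.** Continuous variables are to be presented as means with confidence intervals, so direction and approximate size would be visible. That sentence covers presentation, however, and names no between-arm comparison.
- **That a fixed power loss follows, or that the main conclusion is weakened.** The loss depends on shift, distribution and cut, none of which is given. It is also calculated for a difference test, while the trial is framed as non-inferiority. The sample size and margin rest on symptom reduction.

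Nor does the protocol single out daily impact as a distinctive or scarcely reported measure. Its remarks of that kind concern patient experience.

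**Conclusion.** The point holds in limited form. A categorical test is the only one named for primary outcomes, two of the outcomes in Table 1 are 0–10 scores, and the sole binary rule does not fit them; for satisfaction it cannot be applied at all. Taken literally, this discards the ordering of the scores or relies on an unstated cut.

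The size is illustrative. Under rounded normal scores, a 0.22 SD shift and a two-sided 5% difference test, about 76–81% power falls to about 61% at best with a cut and to 38–42% with the full table. At 0.30 SD the loss is about 10 to a little over 20 points; with a poorly placed cut it can exceed 50. These figures are not a bound.

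The correction is worth making before analysis. It does not touch the 330 per arm or the symptom-based non-inferiority result.

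**What to change.** In the Statistical analysis section:

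1. Limit chi-square/Fisher to the yes/no outcomes: binary symptom success, complications and recurrence.
2. Analyse impact and satisfaction separately, each on its 0–10 scale. The two run in opposite directions, so the 0–20 total in Table 1 should not stand in for them. Report the between-arm mean difference (SCL minus RBL) with its 95% confidence interval from a linear model, with a Wilcoxon or proportional-odds analysis as a check.
3. Adjust impact for its baseline value where one is collected. Compare satisfaction post-treatment only, with no reduction rule.
4. State whether the two items are primary or secondary, and align the abstract, Objectives, Table 1 and Table 2.

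This costs a few sentences and a consistent outcome list. It needs no new data and no more patients.

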## Methods and analysis

### Trial design

The THROS trial is a non-inferiority, multicentre, randomised controlled trial with two parallel groups: RBL vs. SCL. The allocation ratio is 1:1. Crossover is possible for patients who experience no improvement of symptoms after at least two treatments within one treatment arm. It is expected that when two treatments have not reduced symptoms and a third treatment is necessary, both patients and surgeons are inclined to try a new treatment option. So crossover rate is also indicative for treatment success. Also, when patients have a strong preference for one of the two treatment arms and refuse randomisation, then registration in the preference arm is allowed. All patients’ symptoms could not be effectively managed by conservative treatment, which included dietary changes, laxatives, and lifestyle improvements. Conservative management was the first step of therapy in all cases. After eligibility has been established and patients have given their written informed consent, allocation or registration to one of the two treatment arms is possible. Data will be analysed on both ‘intention to treat’ and ‘per protocol’ basis.

The trial was registered at the Dutch Trial Register (NL8377). The protocol was drafted in accordance with the Standard Protocol Items: Recommendations for Interventional Trials statements (SPIRIT) [12].

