### Sample size calculation

The sample size is based on a success percentage of 70% in both treatment arms, in terms of symptom reduction. Based on the available literature from Cocorullo et al. [6], we will perform a non-inferiority analysis with a two-sided significance (alpha 2.5%), 80% power and a 10% non-inferiority limit. Consequently, a total of 330 randomised patients are required per arm, so 660 randomised patients in total.Significance level (a) = 2.5%Power (1-beta) = 80%Non-inferiority limit = 10%Proportionality group A = 70%Proportionality group B = 70%Sample size required per group = 330Total sample size required = 660

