## Discussion

The THROS study is the first large multicentre randomised trial to study the difference in effectivity between RBL and SCL for the treatment of grade 1–2 HD. Primary and secondary outcomes consist of both objective and subjective patient-reported outcomes. In this non-inferiority trial, we hypothesize that SCL is non-inferior to RBL with regard to effectiveness, patient experience, complications and recurrences.

As HD is one of the most common conditions in the general population, with an annual incidence of 5%, it represents a significant epidemiologic and economic burden. Most patients experience blood loss and for some patients, this blood loss can cause symptomatic anaemia. Patients with grade 1–2 haemorrhoids may also experience other symptoms like itchiness, pain or soiling and, because of additional stigma and shame, it represents a high burden that affects the quality of life.

However, patients’ experience of HD symptoms and its burden on everyday life is in contrast with the surgeon’s experience in which it is perceived as a ‘simple’ diagnosis with a relatively ‘simple’ solution/treatment. Therefore, surgeons and proctologists are driven to treat their patients with less invasive, but most effective method, in which the patients’ experience of the treatment also plays an important role. This is especially so considering that for the majority of cases, a singular treatment is insufficient to fully treat the HD.

In case of more severe (grade 3–4) or recurrent HD, there are several multicentre randomised controlled trials studying the effect of different treatment options. Both the HollAND and Napoleon trial, which were forced to stop prematurely due to inclusion difficulties, are currently in the follow-up phase. Both studies compare more invasive techniques (haemorrhoidectomy or sutured mucopexy) with RBL [14, 15]. However, symptomatic grade 1–2 HD are far more common in the general population and so an answer as to what the best and most appropriate minimal invasive treatment option is, is needed.

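### The Statistical analysis section does not carry out the promised non-inferiority analysis: it names tests of no difference and never uses the 10-point limit

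*Protocol article*

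**What the plan says.** Under Trial design: "The THROS trial is a non-inferiority, multicentre, randomised controlled trial with two parallel groups: RBL vs. SCL". The Discussion gives the direction: "we hypothesize that SCL is non-inferior to RBL with regard to effectiveness, patient experience, complications and recurrences".

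Sample size calculation commits to a margin-based analysis: "we will perform a non-inferiority analysis with a two-sided significance (alpha 2.5%), 80% power and a 10% non-inferiority limit". The limit is tied to one endpoint: "The sample size is based on a success percentage of 70% in both treatment arms, in terms of symptom reduction". The result is 330 per arm, 660 in total.

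Statistical analysis, the only section that describes the analysis, reads differently. For the primary outcomes: "Analysis of primary outcomes will be tested with chi-square test or" Fisher's exact test. The criterion is a p-value "of 0.05 or less is considered as statistically significant". The section does not mention the 10-point limit, a null hypothesis shifted by the limit, or a rule for concluding non-inferiority. Confidence intervals are planned for means of continuous variables; categorical variables are to be shown as percentages. Both intention-to-treat and per-protocol analyses are planned.

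**The concern.** A chi-square or Fisher test asks whether the two proportions differ at all. Non-inferiority asks whether a deficit of 10 points or more can be ruled out. A non-significant test of no difference does not rule it out; it may only mean that the data are too imprecise to tell. The promise in Sample size calculation and the test in Statistical analysis therefore answer different questions.

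At stake is the main conclusion. An analyst who follows Statistical analysis obtains a p-value that does not address the hypothesis, with no other criterion in that section. The easy next step is to report no significant difference as if it meant not inferior. That step is most likely to mislead when fewer patients are analysed, because non-significance then becomes easier to reach.

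**Working it through.** **Inputs.** Success 70% in each arm, limit 10 points, alpha 2.5%, power 80%, 330 per arm (Sample size calculation); 1:1 allocation (Trial design); p of 0.05 or less (Statistical analysis). The true SCL rates of 65% and 60% are scenarios chosen for this check: half the limit and the full limit below 70%.

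**Step 1: reproduce the plan's figure.** For a one-sided test against the limit,

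n per arm = (z_alpha + z_beta)² × [p_A(1 − p_A) + p_B(1 − p_B)] / limit²

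= (1.960 + 0.842)² × (0.21 + 0.21) / 0.10² = 329.7, so 330.

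This matches. It requires a one-sided 2.5%. Taking the words two-sided alpha 2.5% literally (one-sided 1.25%) gives 400 per arm. The trial was therefore sized for a one-sided 2.5% test of the margin, which is the same as comparing the lower limit of a two-sided 95% confidence interval with −10 points.

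**Step 2: compare the two rules at 330 per arm.** Exact binomial enumeration, RBL success 70%. Rule A is a Pearson chi-square without continuity correction, p > 0.05. Rule B is the lower limit of the two-sided 95% Wald interval for SCL minus RBL lying above −10 points.

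| True SCL rate | A: non-significant | B: non-inferior | Non-significant but fails the margin |
|---|---|---|---|
| 70% (equal) | 95.0% | 80.1% | 17.4% |
| 65% (5 points worse) | 72.0% | 28.0% | 44.1% |
| 60% (10 points worse) | 22.9% | 2.5% | 20.5% |

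In the last row, rule B holds the planned 2.5% error. Rule A, if it were read as non-inferiority, would be wrong about nine times as often (22.9 / 2.5 = 9.2).

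**Step 3: effect of fewer patients.** With 165 per arm (illustrative, half the plan) and SCL 10 points worse, rule A rises to 52.1% and rule B stays at 2.5%.

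**Step 4: one example data set.** RBL 231/330 = 70.0%, SCL 211/330 = 63.9%.
- Difference = −6.06 points.
- Pooled standard error = 3.661 points, z = −6.06 / 3.661 = −1.655, p = 0.098: no significant difference.
- Unpooled standard error = 3.654 points, 95% interval = −6.06 ± 1.960 × 3.654 = −13.2 to +1.1 points. The interval includes −10, so non-inferiority is not shown.

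**Step 5: the exception.** A significant chi-square in favour of SCL does imply non-inferiority. With equal arms this happens in about 2.5% of trials.

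**The case against.** The strongest reply is that the article does promise a non-inferiority analysis with a 10% limit, in Sample size calculation, and that an article may leave the details to a statistical analysis plan. The first half stands. It would be too strong to say that the trial, as written, never intends to test its hypothesis; the defect is that one section does not carry out the other. The second half does not rescue the text. The article is not silent on the primary test. It names one, and that test does not match the question.

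A reader might also infer three stronger points, which the document does not support:

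- **That the investigators will treat p > 0.05 as proof of non-inferiority.** No section says so. The percentages for rule A depend on that reading, which the text invites but does not state.
- **That the 0.05 level is itself an error.** It is not. A two-sided 95% interval corresponds to the one-sided 2.5% that reproduces 330 per arm.
- **That the primary analysis is wrong because it is unadjusted, or because of the sentence** "Significant confounders will be identified using multivariate analysis". Choosing covariates by significance is open to criticism, but the section does not say that this step decides the primary result. Randomisation is unstratified (Recruitment and blinding), so an unadjusted difference in proportions is a valid primary estimate. Adjustment is a separate and optional matter.

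A further fair objection is that a margin rule alone cannot be executed. There are three post-baseline assessments, and none is named as primary. Treatment efficacy defines improvement as any fall on the symptom scale with a maximum of 25, whereas Statistical analysis refers to a reduction per symptom. This stands, and the fix takes it up.

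**Conclusion.** The point holds as a mismatch between two sections. The test named for the primary outcomes cannot establish the stated hypothesis unless SCL turns out significantly better, and no margin-based rule replaces it. This should be corrected before analysis.

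The size of the risk is conditional. If non-significance were taken as non-inferiority, the false-claim rate at a true 10-point deficit would be 22.9% instead of 2.5%. At a 5-point deficit, 72.0% of trials would be called not different while only 28.0% would meet the margin. These figures assume 330 analysed per arm, an RBL success rate of 70%, an uncorrected chi-square and a Wald interval. A continuity correction or Fisher's test would be non-significant at least as often.

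**What to change.** In Statistical analysis, for the binary symptom-improvement endpoint on which the trial is sized, replace the chi-square/Fisher test with text such as:

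*The difference in success proportion (SCL minus RBL) will be estimated with a two-sided 95% confidence interval at [one named time point], with improvement defined as [one definition]. Non-inferiority will be concluded only if the lower limit lies above −10 percentage points in both the intention-to-treat and the per-protocol set.*

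Three further changes belong with it:

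- Choose one definition of improvement, total score or per symptom, and use it in both Treatment efficacy and Statistical analysis.
- Report recurrence and complications, which are also listed as primary outcomes, as differences with 95% confidence intervals. Do not claim non-inferiority for them from a non-significant test, because the 10% limit is set for symptom reduction only.
- Describe the alpha in Sample size calculation as one-sided 2.5%, since that is what gives 330.

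Adjustment, for example for baseline PROM score, may be added if pre-specified, but this correction does not require it.

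The cost is wording plus two decisions (time point and definition), to be made before outcome data are compared between arms. No new patients or data are needed: 330 per arm gives 80.1% power at 70% v 70%.
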